## **7. Interim Analysis**

Not applicable.

## **8. Data Analysis Plan**

### **8.1 Recruitment and representativeness of recruited patients**

A CONSORT-style flow chart will be constructed based on aggregated data. This will include the following: (1) the number of eligible patients; (2) the number of patients who agree to enter the trial with a brief description of the reasons; (3) the number of patients who are randomized and undergo follow-up; (4) the number of patients who withdraw in any period of this trial; (5) the number of patients lost to follow-up; and (6) the number of patients excluded or analyzed.

### **8.2 Baseline characteristics**

#### **8.2.1 Demographics**

A table will present the overall baseline characteristics of the patients.

One table each will present the baseline characteristics of patients with renal tumors and patients with prostate cancer. The demographic data will include the age (years), sex, height (m), weight (kg), and body mass index (BMI, kg/m^2) of the patients.

### **8.2.2 Characteristics of tumor or the target organ**

For renal tumors, the R.E.N.A.L. score will be reported. For prostate cancer, the volume of the prostate and the Gleason score will be reported. These factors, along with the BMI, can influence and reflect the difficulty level of the surgery.

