### 3.2 Sample Size

According to the requirements of the "Guideline for the Design of Clinical Trials of Medical Devices" (published by CFDA), the number of trial cases was inferred based on the non-inferiority sample size

calculation method, and the number of cases was calculated through joint discussion by clinical trial institutions, major researchers, and statistical analysts.

The formula is as follows:

$$n_T = n_C = \frac{(Z_{1-\alpha/2} + Z_{1-\beta})^2 [P_C(1-P_C) + P_T(1-P_T)]}{(|D| - \Delta)^2},$$

where  $\alpha = 0.025$  (one-sided),  $\beta = 0.2$  (80% confidence), and the non-inferiority margin  $\Delta = 10\%$ . Assuming that the surgical success rate of the experimental group and the control group is equal, the expected surgical success rate of the two groups is 98% (i.e.,  $P_T = P_C = 98\%$ ). As the ratio between the two groups is 1:1, 31 subjects are needed in each group. Considering that the dropout rate of subjects during the trial is about 10% or more, this study plans to enroll 68 subjects, with 34 in the experimental group and 34 in the control group. If the dropout rate exceeds the expected 10%, resulting in insufficient valid data, the number of patients enrolled can be appropriately increased, and the proposed increase in the number of patients enrolled should be filed with the Ethics Committee of Chinese PLA General Hospital.

Urologic surgery is divided into upper and lower urinary tract surgeries. In this clinical trial, representative surgical methods of partial

nephrectomy and prostatectomy are selected for surgery. In the end, partial nephrectomy and prostatectomy in this scheme is no less than 30%, and each clinical center ensures that subjects are operated on for both partial nephrectomy and prostatectomy surgery. This information will be summarized after the end of the trial. According to the non-inferiority test, when the lower limit of the 95% confidence interval of the difference in surgical success rate between the two groups is  $> -10\%$ , the non-inferiority hypothesis is established, which can be considered to meet the qualified requirements of this clinical trial.

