### **3.3 Randomization**

This study will adopt a random number distribution system. The random grouping table of subjects will be generated by independent statisticians (who will not participate in the clinical trial) from random coding units. The ratio of the test group to the control group will be 1:1. The seed number for generating the random table is fixed, and the process of generating the random table can be repeated. The generated random table of subjects will be imported into the random system by the random system administrator. All random numbers will not be used twice. After the successful screening of subjects, the random responsible person of each center will log in to the system and enter the basic information of

subjects according to the system prompts, including the date of birth and the name abbreviation, etc. The system will generate a unique random number for each subject and randomly allocate subjects to the groups.

We used stratified randomization with random block sizes of four.

Stratification was identified by the surgery type (prostatectomy and partial nephrectomy) with the randomization conducted separately for each stratum.

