#### **4.2.2 Perioperative morbidity**

To assess perioperative morbidity, the following clinical data will be collected:

1. Surgery-associated factors: intraoperative blood loss, operative time, and warm ischemia time (for partial nephrectomy).
2. Complications and adverse events: Adverse events will be recorded

using the Clavien-Dindo classification at 4 weeks and 6 weeks postoperatively.

3. Postoperative hospitalization days.
4. Length of days in critical care.
5. Reoperational intervention.
6. Readmission to the hospital: Readmission to the hospital for any reason will be recorded, and the surgery-associated condition will be systemically reviewed.
7. Intra- and postoperative blood transfusion rates.
8. Mortality rate.

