### **8.3.2 Secondary outcomes analysis**

The differences in secondary outcomes will be compared as follows:

- (1) Categorical data: logistic regression (with Firth's correction) or Exact Fisher's test;
- (2) Continuous data: linear regression

The hospital or surgery type can be used as adjusting factors.

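### Cheap improvement: the SAP names baseline measures of surgical difficulty but leaves them out of the models for operative time, blood loss and warm ischemia time, which costs precision but not validity

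*Combined protocol and SAP*

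**What the plan says.** SAP 8.2.2 sits under baseline characteristics. "For renal tumors, the R.E.N.A.L. score will be reported"; "For prostate cancer, the volume of the prostate and the Gleason score will be reported". The section then adds: "These factors, along with the BMI, can influence and reflect the difficulty level of the surgery". It gives these variables no further role.

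SAP 8.3.2 has one rule for every continuous secondary outcome, "Continuous data: linear regression", and one sentence on adjustment: "The hospital or surgery type can be used as adjusting factors". The adjustment is optional, and no difficulty variable is named for any model.

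SAP 4.2.2 makes blood loss, operative time and, for partial nephrectomy, warm ischemia time secondary outcomes. On allocation, SAP 3.3 says: "Stratification was identified by the surgery type (prostatectomy and partial nephrectomy) with the randomization conducted separately for each stratum". Nothing balances difficulty within a procedure.

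Protocol 3.4.3 ties one of these variables to the extent of surgery: pelvic lymph node dissection is added to a prostatectomy when the biopsy Gleason score is 4+3 or higher.

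**The concern.** The plan identifies likely predictors of how hard an operation will be and does not use them for the outcomes they should predict. None of the three outcomes has a preoperative value of its own to adjust for. Surgery type removes the difference between procedures but not a run of complex tumours or large prostates in one arm. For warm ischemia time, measured in one procedure only, surgery type is constant and adjusts nothing.

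At stake is the width of the confidence intervals for these comparisons in a 68-patient trial, and what can be done if the baseline tables show an imbalance. The surgical team is not blinded and the SAP has no rule for this case, so an adjustment chosen after seeing the imbalance would be open to challenge.

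**Working it through.** **The plan's own figure.** The documents give no power, SD or sample size for these three outcomes. The only figure to reproduce is for the primary outcome, where "the expected surgical success rate of the two groups is 98"%: (1.96 + 0.842)² × 2 × 0.98 × 0.02 / 0.10² = 30.8, so 31 per group, as stated. It does not bear on this point.

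**Inputs from the documents.**
- 68 patients, 1:1, and at least 30% for each procedure (SAP 3.2). 0.30 × 68 = 20.4, so each procedure has 21 to 47 patients.
- Pooled models for operative time and blood loss: p = 3 covariates (BMI, R.E.N.A.L. score, prostate volume), or p = 4 with a Gleason category.
- Warm ischemia time: p = 2 (R.E.N.A.L. score, BMI).

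**Assumed input.** R², the share of outcome variance that the covariates explain, is not in the documents. I use 0.16-0.25 (multiple correlation 0.4-0.5) and show 0 as the worst case.

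**Precision.** The adjusted variance of the arm difference relative to the unadjusted is (1 − R²)(N − 3)/(N − p − 3).

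| Model | (N − 3)/(N − p − 3), i.e. R² = 0 | R² = 0.16 | R² = 0.25 |
|---|---|---|---|
| Pooled, N = 68, p = 3 | 65/62 = 1.05 | 0.88 | 0.79 |
| Pooled, N = 68, p = 4 | 65/61 = 1.07 | 0.90 | 0.80 |
| Warm ischemia, N = 47, p = 2 | 44/42 = 1.05 | 0.88 | 0.79 |
| Warm ischemia, N = 21, p = 2 | 18/16 = 1.12 | 0.94 | 0.84 |

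Simulated linear models (8,000 replicates per cell) gave 1.12, 0.94 and 0.86 for N = 21, and 1.05, 0.88 and 0.79 for N = 47. I take the more cautious 14% as the upper end of the gain with 21 patients.

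**Break-even.** The variance ratio equals 1 at R² = p/(N − 3): 3/65 = 0.05 and 4/65 = 0.06 pooled, and 2/17 = 0.12 with 20 patients. On the confidence-interval scale, where fewer degrees of freedom also widen the t quantile, break-even is about 0.05 (pooled, three covariates) and about 0.13 (20 patients).

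**Chance imbalance.** The standardized difference between arms in a baseline covariate has SD 2/√N. The two-sided normal chance that it exceeds 0.5 SD is:
- N = 68: SD 0.24, about 4%
- N = 47: SD 0.29, about 9%
- N = 21: SD 0.44, about 25%

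The first line applies to operative time and blood loss, the other two to warm ischemia time. An imbalance of 0.5 SD in the combined covariate score moves the unadjusted difference by 0.5 × 0.4 to 0.5 × 0.5, i.e. 0.20-0.25 SD of the outcome.

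**Validity.** In simulation with no true effect (10,000 runs per setting; N = 20, 34, 48; R² = 0.1 and 0.3), the unadjusted test rejected in 4.5-5.2% of runs overall. In runs with an imbalance above 0.5 SD it rejected in 6-10% at R² = 0.1 and 11-17% at R² = 0.3. The adjusted test stayed at 4-6% in the same runs.

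**The case against.** The strongest case against is that this is an efficiency preference, not an error. Saying that a factor affects difficulty does not commit the plan to adjust for it. Randomization makes the unadjusted difference unbiased, and its confidence interval already allows for chance imbalance. The outcomes are secondary, the SAP calls the trial exploratory, and no margin or success criterion rests on them. Baseline tables by procedure will show any imbalance. All of this stands, and it is why the point is only an improvement.

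The benefit also depends on an R² that the documents do not supply. With about 20 partial nephrectomies and weak covariates, adjustment could lose precision. BMI may add little, because protocol 7.1 restricts it to 18-30 kg/m². This stands too, and the break-even values mark the limit.

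There is a practical objection. The protocol's assessment table has no separate item for R.E.N.A.L. score or prostate volume, only the lesion CT/MR, and SAP 6.1 does not impute missing data other than the primary outcome unless otherwise specified. An adjusted model without a missing-value rule would drop patients. The fix needs such a rule.

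The objection does not remove the gap. SAP 8.3.2 gives no way to use variables that the trial already plans to report, and surgery type cannot stand in for them within a procedure.

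**Conclusion.** The point holds as a modest loss of efficiency in three secondary comparisons. Under an assumed R² of 0.16-0.25, adjustment would cut the variance of the arm difference by about 12-21% in the pooled models (10-20% with a Gleason category added), and for warm ischemia time by about 6-14% with 21 patients and 12-21% with 47. It would also guard against a chance imbalance above 0.5 SD, which has a probability of about 4% pooled and 9-25% for warm ischemia time.

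Three stronger readings are tempting, and the documents do not support them:
- A reader might infer that the planned comparisons are biased, so that a false slowing is created or a real one hidden. They are not: error is about 5% overall, and only the error conditional on a marked imbalance is raised.
- A reader might apply the 25% imbalance risk to all three outcomes. It belongs to warm ischemia time alone, and only if partial nephrectomies fall to the 30% minimum.
- A reader might see a contradiction between SAP 8.2.2 and 8.3.2. There is none; the second section simply does not use what the first describes.

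The primary non-inferiority conclusion is unaffected.

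**What to change.** In SAP 8.3.2, prespecify:
- **Operative time and blood loss:** arm + surgery type + BMI + difficulty covariates nested within surgery type. These are R.E.N.A.L. score for partial nephrectomy, and prostate volume and preoperative biopsy Gleason category (4+3 or higher, or lower) for prostatectomy. Nesting is needed because each score exists for one procedure only. The Gleason value must be the biopsy one; the specimen value in SAP 4.2.3 is an outcome.
- **Warm ischemia time (partial nephrectomy only):** arm + R.E.N.A.L. score + BMI.
- **Missing baseline covariates:** replace with the mean within the procedure, so that no patient leaves the model, and state this as an exception to SAP 6.1.
- **Reporting:** give the unadjusted difference alongside.

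The cost is SAP wording, making sure that the scores are recorded at baseline, and two to four degrees of freedom. If the covariates explained nothing, variance would rise by about 12% with 21 patients and by about 5-7% in the pooled models.

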## **8.3 Efficacy analysis**

### **8.3.1 Primary outcome analysis**

The primary outcome will be analyzed by a non-inferiority analysis. According to the medical statistics scenario, the main efficacy evaluation is based on the intention-to-treat population set and per-protocol population set. The statistical description and inference will be based on the characteristics of the data, and the appropriate descriptive indicators and hypothesis testing methods will be selected.

The primary efficacy indicator of surgical success rate uses a non-inferiority test, with the following hypotheses tested:

Null hypothesis:  $H_0: PT - PC \leq -\Delta$ ;

Alternative hypothesis:  $H_1: PT - PC > -\Delta$ .

At  $\alpha = 0.025$  (one-sided test) and  $\beta = 0.2$  levels, the success rates of the two groups will be statistically described and compared, and the 95% confidence interval (CI) of the difference in success rates between the two groups will be calculated. If the lower limit of the 95% CI of the difference in success rates between the two groups is greater than the non-inferiority margin ( $-\Delta$ ), it can be concluded that the experimental group is non-inferior to the control group.

The difference in the primary outcome (success rate) between the telesurgery and local surgery groups will be compared using the Miettinen-Nurminen method or Newcombe-Wilson score method test, according to the success rate data. The tipping assay can be used to determine the robustness and sensitivity the statistical conclusion.

### **8.3.2 Secondary outcomes analysis**

The differences in secondary outcomes will be compared as follows:

- (1) Categorical data: logistic regression (with Firth's correction) or Exact Fisher's test;
- (2) Continuous data: linear regression

The hospital or surgery type can be used as adjusting factors.

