### 9.2 Sample Size Determination

According to the requirements of the "Guideline for the Design of Clinical Trials of Medical Devices" (published by CFDA), the number of trial cases was inferred based on the non-inferiority sample size calculation method, and the number of cases was calculated through joint discussion by clinical trial institutions, major researchers, and statistical analysts.

The formula is as follows:

$$n_T = n_C = \frac{(Z_{1-\alpha/2} + Z_{1-\beta})^2 [P_C(1-P_C) + P_T(1-P_T)]}{(|D| - \Delta)^2},$$

where  $\alpha = 0.025$  (one-sided),  $\beta = 0.2$  (80% confidence), and the non-inferiority margin  $\Delta = 10\%$ . Assuming that the surgical success rate of the experimental group and the control group is equal, the expected surgical success rate of the two groups is 98% (i.e.,  $P_T = P_C = 98\%$ ). As the ratio between the two groups is 1:1, 31 subjects are needed in each group.

Considering that the dropout rate of subjects during the trial is about 10% or more, this study plans to enroll 68 subjects, with 34 in the experimental group and 34 in the control group. If the dropout rate exceeds the expected 10%, resulting in insufficient valid cases, the number of participants can be appropriately increased, and the number of the total valid cases should not be higher than 34 of each trial group. The increase in the number of patients enrolled should be filed with the Ethics Committee of Chinese PLA General Hospital.

Urologic surgery is divided into upper and lower urinary tract surgeries. In this clinical trial, representative surgical methods of partial nephrectomy and prostatectomy are selected for surgery. In the end, partial nephrectomy and prostatectomy in this scheme is no less than 30%, and each clinical center ensures that subjects are operated on for both partial nephrectomy and prostatectomy surgery. This information will be summarized after the end of the trial. According to the non-inferiority test, when the lower limit of the 95% confidence interval of the difference in surgical success rate between the two groups is  $> -10\%$ , the non-inferiority hypothesis is established, which can be considered to meet the qualified requirements of this clinical trial.

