#### **4.2.1 Early recovery**

The following tools will be used to measure the early recovery:

1. Overall functional recovery: Quality of recovery 15-item score (QoR-15 score) at baseline (preoperative), 4 weeks, and 6 weeks.
2. Overall functional recovery for prostate cancer patients: Expanded Prostate Cancer Index Composite-26 (EPIC-26 score) at baseline (preoperative), 4 weeks, and 6 weeks.
3. Physical activity: 30-second chair-to-stand test (number of times the patient can stand from sitting in a 30-second interval) at baseline (preoperative), 4 weeks, and 6 weeks.

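### SAP 8.3.2 does not prespecify baseline adjustment for the three continuous secondary outcomes measured before surgery, and it leaves the randomization stratum as an optional covariate

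*Combined protocol and SAP*

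**What the plan says.** SAP 8.3.2 covers all continuous secondary outcomes in one line, "2) Continuous data: linear regression". The only statement on covariates is "The hospital or surgery type can be used as adjusting factors". That sentence permits no covariate, either one, or both, and gives no rule for choosing. Protocol 9.1 refers to the SAP for analysis detail and adds none.

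SAP 4.2.1 schedules the recovery measures before surgery and at two later visits, for example "QoR-15 score) at baseline (preoperative), 4 weeks, and 6 weeks". EPIC-26 (prostate cancer patients) and the 30-second chair test follow the same schedule. Neither document says whether the response is the follow-up value or the change from baseline, whether the baseline value enters the model, or how the two visits are handled.

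SAP 3.3 describes block randomization within strata: "Stratification was identified by the surgery type (prostatectomy and partial nephrectomy").

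**The concern.** A pre-operative score usually predicts the post-operative score on the same scale. If it is left out of the model, chance baseline imbalance goes uncorrected and the interval is wider than it need be. The planned size was set for the success rate alone, so the secondary comparisons have only the precision that 34 per arm happens to give, and EPIC-26 has fewer patients than that.

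Prostatectomy and partial nephrectomy are pooled for operative time, blood loss, hospital stay and task load. Stratified randomization balances the arms on operation. A model that omits the operation nevertheless counts the between-operation difference as noise, so it reports too large a standard error.

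The researchers are not blinded (protocol 3.3). With the covariate set open, a reader of the results cannot tell whether the reported model was the one intended.

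**Working it through.** **The plan's own figure.** Inputs from protocol 9.2: "the expected surgical success rate of the two groups is 98"%, margin 10 points, one-sided 0.025, power 80%, 1:1 allocation. With z values 1.960 and 0.842:

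n = (1.960 + 0.842)² × (2 × 0.98 × 0.02) / 0.10² = 7.849 × 0.0392 / 0.01 = 30.8, rounded up to 31.

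This matches "31 subjects are needed in each group". Allowing for 10% dropout, 31 × 1.1 = 34.1 and 31 / 0.9 = 34.4, against the 34 per arm planned. The calculation concerns the primary outcome only. No precision or power figure is given for any secondary outcome.

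**Baseline adjustment (QoR-15, chair test, EPIC-26).** Let r be the correlation between baseline and follow-up; it is not in the documents, and 0.3 to 0.7 is assumed. Adjustment multiplies the variance of the arm difference by 1 − r². The difference detectable at 80% power, two-sided 5%, by normal approximation, is 2.80 × √(2/m) × √(1 − r²) SD with m per arm.

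| r | Variance factor | Standard error factor | 34/(1 − r²) | Detectable, m = 34 |
|---|---|---|---|---|
| 0 | 1.00 | 1.00 | 34 | 0.68 SD |
| 0.3 | 0.91 | 0.95 | 37.4 | 0.65 SD |
| 0.5 | 0.75 | 0.87 | 45.3 | 0.59 SD |
| 0.7 | 0.51 | 0.71 | 66.7 | 0.49 SD |

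So the variance falls by 9%, 25% or 49%. With 31 per arm the detectable difference goes from 0.71 SD to 0.68/0.62/0.51 SD.

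The head counts in the table do not apply to EPIC-26. If the 30% minimum in protocol 9.2 is read as applying to each operation, prostatectomy makes up 30% to 70% of patients, or about 10 to 24 per arm (0.3 × 34 = 10.2; 0.7 × 34 = 23.8). At r = 0.5 the detectable difference then falls from 1.25 to 1.09 SD with 10 per arm, and from 0.81 to 0.70 SD with 24 per arm.

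A simulation of 68 patients, 6,000 null trials per scenario, gave mean standard errors of 0.242 without and 0.232 with baseline at r = 0.3, and 0.241 and 0.211 at r = 0.5. The ratios, 0.96 and 0.88, are close to the formula.

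The open choice of response also matters. In units of the unadjusted variance, an unadjusted change score has variance 2(1 − r) = 1.4/1.0/0.6, which is worse than adjustment at every assumed r.

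**Stratum.** Let the operations differ by d within-type SDs (assumed), with a share p of one type. The pooled residual variance is 1 + p(1 − p)d² times the within-type variance, so the unadjusted standard error is too large by the factor √(1 + p(1 − p)d²).

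| d | p = 0.5 | p = 0.3 |
|---|---|---|
| 0.5 | √1.0625 = 1.03 | √1.0525 = 1.03 |
| 1.0 | √1.25 = 1.12 | √1.21 = 1.10 |
| 1.5 | √1.5625 = 1.25 | √1.4725 = 1.21 |

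The simulation used two equal strata and blocks of four. It gave 0.258 / 0.250 = 1.03 at d = 0.5 and 0.279 / 0.250 = 1.12 at d = 1. At d = 1 the unadjusted test rejected in about 3% of null trials instead of 5%, so it is conservative.

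**Choice of model.** The same simulation, with five hospitals, took the smallest p-value over the four permitted covariate sets (none, surgery type, hospital, both). The two-sided error rose from 5% to about 6.4–7.2% for one outcome at one visit. If including or omitting baseline is also left open (eight models), it rose to about 8–11%.

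**The case against.** The strongest reply is that nothing here is wrong, only unstated. Linear regression does not exclude a baseline term, and an analyst may well include one. A fixed unadjusted comparison in a randomized trial is valid. These are secondary outcomes without power claims, in a trial that SAP section 3 calls exploratory. The losses depend on quantities the documents do not give, and at the low end they are slight: 34 patients per arm become equivalent to 37, or the standard error is 3% too large.

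All of that stands, and it limits the point in three ways.

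- A reader might infer that the plan has decided to ignore baseline. The SAP is silent, so the loss arises only if baseline is in fact left out.
- A reader might extend the baseline point to every continuous outcome. Only three have a pre-operative value. Blood loss, operative time, warm ischemia time, stay and task load have none.
- A reader might extend the stratum point to every outcome. EPIC-26, warm ischemia time and lymph node count each come from one operation, so surgery type is constant there.

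What the reply does not answer is that the trial already collects the baseline values and already stratifies by operation. Using both costs nothing, and no text elsewhere in the protocol or SAP closes the gap.

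**Conclusion.** The point holds as one of prespecification and precision. Baseline adjustment is not specified for QoR-15, EPIC-26 and the chair test, and the stratum is optional where both operations contribute.

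The likely cost ranges from slight to substantial. Adjustment for baseline would bring the variance to 0.91, 0.75 or 0.51 of its unadjusted value at assumed correlations of 0.3, 0.5 or 0.7. Omitting the stratum overstates the standard error by about 3%, 12% or 25% at assumed differences of 0.5, 1 or 1.5 SD with an equal mix, or 3%, 10% or 21% at 30:70.

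A reader might conclude that the secondary comparisons would be invalid. They would not be: an unadjusted analysis keeps its type I error, and is conservative when the stratum matters. Inflation arises only if the model is picked on results, and nothing in the documents says that it will be. The primary non-inferiority analysis in SAP 8.3.1 does not depend on any of this. The change should be made, but the trial's main conclusion does not hang on it.

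**What to change.** Replace item (2) of SAP 8.3.2 and the sentence on adjusting factors with a statement by outcome:

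- **QoR-15 and the 30-second chair test:** linear regression of the follow-up value at each visit on arm, the baseline value of the same measure, and surgery type.
- **EPIC-26:** the same model without surgery type, since only prostatectomy patients contribute.
- **Operative time, blood loss, stay and task load:** arm and surgery type.
- **Warm ischemia time and lymph node count:** arm, without surgery type.

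Make surgery type mandatory rather than permitted wherever both operations contribute, and label any model with hospital as a sensitivity analysis. A joint repeated-measures model over weeks 4 and 6 is an option, not a requirement. For categorical outcomes, keep Fisher's exact test as the stated fallback for rare events.

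The cost is SAP wording, agreed before the outcome data by arm are examined. No new data are needed.
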